### Intervention (INDI program)

INDI is a multi-component program based on the chronic care model and previous collaborative care programs adapted to the conditions of primary care in the Catalan public healthcare system. It is made up of training, clinical and organizational components, as well as health education for patients. Its objective is to improve clinical management and clinical outcomes in depression. The program focuses on how the approach to depression is managed by the primary care team, and introduces the role of the care manager, enhances the relationship between different levels of care, strengthens the skills of the healthcare professionals involved, and empowers patients. It is based on the optimization of available resources rather than the need for additional resources. The characteristics of this program have been published previously [17, 20].

The INDI model has been tested in a clinical trial in which its clinical efficacy was found to be comparable to that reported in the scientific literature for similar interventions, with an effect size of 0.35 compared to standard treatment and depression response and remission rates 15–20% greater during 12 months of follow-up [17]. In a 3-year analysis, an attenuation of the effect parallel to the decrease in the adherence of professionals to the INDI program was observed, in the absence of an active strategy to promote the sustainability of the program [21].

In addition to clinical effectiveness, economic impact is a considerable factor in the decision to implement a healthcare intervention. The evaluation of this parameter showed an incremental cost-effectiveness ratio of €4056/quality-adjusted life year (QALY) or €4.5/depression-free day. This means that INDI yields better results than standard treatment for a modest increase in cost, which translates into a favorable cost-effectiveness ratio according to commonly accepted criteria in the field of healthcare innovation [22].

Although it was not part of the original INDI model, the current model incorporates a new tool for optimizing the clinical management of major depression. This is an interactive clinical guideline integrated in the computerized primary care clinical records. It has been developed based on the most recent clinical practice guidelines for major depression [23, 24] It assists physicians with decisions regarding diagnosis, treatment, and monitoring of major depression; systems for recording and retrieving information on a patient’s clinical status; and automated alerts for clinical situations showing poor control of the illness or risk factors [25, 26].

### Intervention (implementation strategy)

We have designed an implementation strategy conceptually based on and framed within the PARIHS model (Promoting Action on Research Implementation in Health Services) [27] (Fig. 2). This theoretical and operational framework defines implementation success as a function of a) evidence that supports the proposed innovation, b) the context in which the change is to be applied, and c) the components of the facilitation that will drive and maintain the change.$$ \mathsf{Successful}\kern0.5em \mathsf{implementation}=\mathsf{f}\ \left(\mathsf{Evidence},\mathsf{Context},\mathsf{Facilitation}\right) $$

**Fig. 2 Fig2:**
[figure not shown]
Conceptual framework for the implementation project (adapted from the PARIHS framework)

The PARIHS framework considers evidence that supports the innovation in a broad sense, encompassing both obvious sources of evidence (i.e., clinical trials, meta-analyses) and tacit evidence from other sources such as the experience, knowledge, and reflections of healthcare professionals who work in the field (and who, ultimately, apply the proposed changes). The needs, opinions, and preferences of the patients who the intervention is intended for are also included as sources of evidence, as well as knowledge of local circumstances and determinants. This broad understanding of evidence with the inclusion of all the project’s stakeholders is necessary to successfully implement lasting changes in healthcare practice.

Existing evidence regarding the effectiveness of collaborative care models and the INDI model in particular is abundant and solid [11, 14, 16, 17]. Through qualitative techniques such as focus groups and in-depth interviews with local leaders in the fields of primary care, mental health, and healthcare innovation, we will obtain and incorporate the tacit knowledge of patients and professionals as well as information on local characteristics into the INDI model.

The context is the setting in which the proposed change will be implemented. Context includes characteristics of the health organization itself (i.e., receptivity, culture of innovation, leadership, standard procedures for evaluating tasks and results, available resources) that favor effective implementation, as well as obstacles that the implementing team should investigate, identify, and manage. One aspect of the context that is extremely favorable to the implementation of the INDI program is that the Catalan health Institute, through the Innòbics program, fosters a culture of innovation and has taken on the implementation of INDI as a priority project.

Facilitation describes the type of support needed to help people change their attitudes, habits, skills, and ways of thinking and working. Facilitators help people understand what they should change and how to change it to achieve the desired outcome. Internal facilitators (in the health organization itself) will be designated as program leaders in each participating center or as regional project leaders (in each of the two participating regions) who will lead the project implementation at the local level.

External facilitation actions will be conducted by the implementing team, including technical support, training, advice, evaluation, feedback, adaptation of the intervention to the local context, accreditation and re-accreditation of centers and professionals, and inter-institutional coordination.

### Control

The centers in the control group will not establish any special treatment practices, but the organization and professionals will offer patients with depression the best care based on standard criteria. As this is a study of implementation under real conditions the centers in the control group will not be prevented from accessing or applying any other initiative for training or healthcare quality improvement that exists in the study period.

### Measurements

We will assess a series of variables and parameters related to the success of the implementation of the intervention in the care practice principally in terms of acceptability (i.e., the perception among patients and providers that the INDI model is agreeable, satisfactory, or useful), effectiveness (i.e., producing better clinical outcomes), penetration (i.e., the INDI model can be successfully used and become integrated within the service setting), and sustainability (i.e., the extent to which the INDI model is maintained within the service setting’s ongoing, stable procedures), and its impact both in the clinical setting and in the health organization through qualitative procedures and quantitative methods [28].

#### Qualitative assessment

Qualitative assessments will provide information on qualitative aspects of the implementation process, its impact on the health organization, and its effects on professionals and patients (Table 1).

**Table 1 Tab1:** Battery of instruments and procedures for the qualitative evaluation of the perceived impact of INDI model implementation in the healthcare organization, among healthcare professionals, and with patients

Scope of assessment	Instrument	Domains	Source	Time
Healthcare organizations	ARCHO (Assessment of Readiness for Chronicity in Health Care Organizations instrument)	Implementation of chronic care models	Clinical management and leaders	Baseline and 12 months
	CPCQ (Change Process Capability Questionnaire)	Strategies used and capacities for change	Clinical management and leaders	Baseline and 12 months
Professionals	Focus groups	Acceptability, perceived utility, pervasiveness in clinical practice, sustainability, difficulties, and areas for improvement	Primary care doctors and care managers	12 months
Patients	IEXPAC (Instrument for Evaluating Patient Experience of Chronic Illness Care)	Experience of the patient with chronic illness	INDI program patients	12 months
	PACIC-D (Patient Assessment of Care for Chronic Conditions-Depression)	Alignment of the care received with the chronic care model and patient-centered care	INDI program patients	12 months
	Focus groups	Acceptability, perceived utility, pervasiveness in clinical practice, difficulties, and areas for improvement	INDI program patients	12 months

##### Qualitative evaluation at the healthcare organization level

ARCHO (Assessment of Readiness for Chronicity in Health Care Organizations) [29] is an instrument for assessing the degree of implementation of chronic care models in healthcare organizations. It is a questionnaire that contributes information for the evaluation of several dimensions: organization, community orientation, care model, patient self-care, support for clinical decision-making, and information systems. In this project, we will use a modified version for depression, which will be completed by regional management departments and primary care centers, as well as by local leaders in chronic disease management and mental health for evaluation at the meso-level (management of organizations, centers, and care programs).

The CPCQ (Change Process Capability Questionnaire) [30] is a questionnaire consisting of 32 items grouped into two domains: the first evaluates the strategies used (and their success or failure), and the second assesses the capacity for change. This instrument will allow us to determine these parameters in relation to the INDI implementation plan as well as aspects of the organizational culture.

##### Evaluation at healthcare professional level

We will conduct focus group research [31] with groups of professionals directly involved in the implementation of the care model: family physicians and primary care nurses (acting as care managers). The objectives of these groups are to evaluate concepts such as program acceptability, perceived utility, and degree of pervasiveness in clinical practice, and to identify difficulties and areas for improvement in the implementation of the model.

There will be a minimum of two focus groups for each professional tier – primary care physicians and nurses (care managers) – and they will continue until enough information is obtained.

##### Evaluation of patient opinions

The patient experience is an extremely valuable indicator in assessing the quality and utility of a health intervention. In a random sample of the depressed patients treated in the INDI program, we will use two questionnaires that yield complementary information:

The IEXPAC scale (Instrument for Evaluating Patient Experience of Chronic Illness Care) [32] measures the experience of patients with chronic diseases, in this case depression, in their interaction with healthcare professionals and services. It assesses the quality of care and the adoption of patient-centered approaches to care.

The PACIC (Patient Assessment of Chronic Illness Care) [33, 34] is a validated instrument in which patients evaluate the extent to which the care they receive is aligned with the chronic care model and patient-centered care. We will use a modified version for depression to assess patients’ experiences as recipients and active users of INDI interventions. We will also obtain information through focus groups. There will be a minimum of two focus groups, which will continue until enough information is obtained.

#### Quantitative evaluation

To measure the impact of the implementation of the model, we will evaluate a battery of quantitatively measurable indicators covering different aspects of quality, performance of the care process, and clinical outcomes: (a) diagnosis and initial evaluation (b) treatment, (c) clinical follow-up, (d) clinical outcomes, and (e) epidemiological indicators (Table 2).

**Table 2 Tab2:** Battery of indicators for the quantitative evaluation of the impact of INDI model implementation on clinical processes and outcomes

Area of evaluation	Indicator	Description
Diagnosis and evaluation	Diagnostic accuracy	The diagnosis of depression in the target population includes specifying the severity of the depressive episode (mild, moderate, severe, or currently in remission) as well as whether it is a single or recurrent episode.
	Diagnostic reliability	DSM-V criteria were used when making the diagnosis (MINI interview)
	Baseline evaluation of severity	In the baseline assessment the severity of symptoms was examined with a validated scale (PHQ9)
	Baseline evaluation of suicide risk	In the baseline assessment the risk of suicide was examined with a validated scale (MINI)
Treatment	Adequacy for mild depression	In mild major depression an antidepressant is not prescribed in the first eight weeks
	Adequacy for moderate or severe depression	In moderate or severe major depression treatment with antidepressants is initiated
	Adequacy for anxiolytic treatment in depression	The prescription of an anxiolytic as the only form of treatment for depression is avoided (i.e., without an antidepressant)
	Adherence to treatment, acute phase	12 weeks after initiating treatment the prescription has not been interrupted
	Adherence to treatment, continuation phase, relapse prevention	6 months after initiating treatment the prescription has not been interrupted
	Intensification of antidepressant treatment: switch	Proportion of new treatments in which the antidepressant is changed
	Intensification of antidepressant treatment: augmentation	Proportion of new treatments in which an antidepressant and an atypical antipsychotic or lithium are concomitantly prescribed
	Intensification of anti-depressant treatment: combination	Proportion of new treatments in which two antidepressants are prescribed simultaneously
Follow-up	Use of a validated scale	Number of times per patient in which a validated scale is used (PHQ9) in clinical follow-up
	Follow-up, after initiating treatment	The patient attends at least one follow-up visit in person in the month following the initiation of antidepressant treatment
	Follow-up, acute phase	The patient attends at least three follow-up visits in the 12 weeks following the initiation of antidepressant treatment
Clinical outcomes	Evolution of the symptoms of depression	PHQ9 descriptive parameters of evolution
	Rate of response to treatment	Proportion of patients who show a reduction ≥50% in their baseline PHQ9 score at 6 and 12 months
	Rate of remission	Proportion of patients with a PHQ9 score < 5 points at 6 and 12 months
	Evolution of functional impact	The descriptive parameter of evolution of GAF scale
	Evolution of suicide risk	Descriptive parameter of the evolution of suicide risk score measured with the MINI suicide risk scale
Epidemiological indicators	Prevalence	Proportion of patients diagnosed with major depression in the population served
	Incidence	New diagnoses of major depression in the population served (annually)
	Rate of antidepressant treatment	Proportion of patients with major depression who receive antidepressant treatment

These indicators will be obtained from the SIDIAP database (Information System for Research in Primary Care) [35], which draws on information from computerized primary care records and other complementary sources.

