## Methods/design

### Aim

The aim of this project is to develop a feasible strategy for the implementation of the INDI model under real healthcare conditions of primary care, initially in a limited geographical area but with the purpose of promoting the generalization of this model in the Catalan public healthcare system.

We will evaluate the success of the implementation based on its perceived acceptability and utility (to patients, professionals, and the organization) and on the integration and sustainability of the program into healthcare practice. The effectiveness of implementation will be assessed in terms of: (a) the quality and precision of the diagnosis of major depression; (b) suicide risk management; (c) the adaptation of the therapeutic management of depression to recommendations based on scientific evidence, including initial treatment selection, treatment duration, and joint management with psychiatry; (d) clinical results in depressed patients; and (e) financial costs associated with implementation.

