### Analyses

The principal analyses will be by intention-to-treat, regardless of the degree of application and adherence to the INDI program guidelines by the patients, professionals, and healthcare centers or areas.

The quantitative analyses of this study will be based on the clinical records of all eligible depressed patients seen in the participating primary care centers. That is, we will work with the entire population and not with a sample, which provides the strengths to minimize selection bias and is based on an independent data collection [36].

At baseline, we will perform a comparative analysis between the areas assigned to the experimental group and the areas of the control group to ensure similarity between the characteristics of their health organizations and clinical practices related to depression.

Analyses of the quantitative variables will consist of both pre-post and intervention-control comparisons of the sets of indicators with quantitative results, with key control points at baseline and at 12 months.

Based on the nature and characteristics of the various questionnaires described in the measures section, the analyses will be carried out in a pre-post comparison framework or as a retrospective analysis at an advanced stage of the implementation process, which we have set at 12 months.

The interviews with focus groups will be recorded and transcribed in their entirety. We will then use a thematic framework analysis to classify and organize the data according to key topics, concepts, and predefined constructs that will be analyzed using qualitative techniques adapted from the normalization process theory [37] to identify barriers and facilitators in the various domains, focusing on ‘hot spots’, for example, dilemmas, conflict situations, and uncertainties.

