However, it is important to recognize the limitations of this project. First, the effect size of the INDI model – and collaborative care models in general – in improving the clinical outcomes of depression is small to moderate. Nevertheless, considering the prevalence and burden of disease that depression represents in society, and in primary care in particular, even this moderate effect could translate into significant benefits not only for individuals with depression, but also for the healthcare system and for society as a whole [15]. Second, it has been established that without measures to maintain the involvement of the professionals and the activities of the INDI program, its performance and its beneficial effects decrease over time [21]. For this reason, our implementation strategy should be seen not as an isolated intervention for initiating the program but as a continuous process. Third, the INDI model is intended exclusively for the management of major depression, although it is commonplace in everyday practice to encounter patients with poorly defined depressive states that do not meet the diagnostic criteria or situations of comorbidity of depression with other common mental disorders [39] – particularly anxiety disorders – or chronic physical illnesses [40, 41]. Further research will be needed to refine and expand the range of objectives of the INDI model and adapt it to the management of instances of complexity and comorbidity.

We anticipate that with this implementation experiment we will see substantial changes in the care process for depression in primary care. Further, we expect the implementation and generalization of the program will have a global impact, which may be highly relevant considering the presence and repercussions of depression on society and its association with suicidal behaviors.

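### The two severity-specific treatment-adequacy indicators can be scored only where severity is known, and recording severity is itself an indicator of INDI's impact

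*Protocol article*

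**What the plan says.** Table 2 (Quantitative evaluation) is titled "Battery of indicators for the quantitative evaluation of the impact of INDI model implementation on clinical processes and outcomes". Two of its treatment rows depend on severity: "In mild major depression an antidepressant is not prescribed in the first eight weeks" and "In moderate or severe major depression treatment with antidepressants is initiated". Its first row, diagnostic accuracy, asks whether the diagnosis "includes specifying the severity of the depressive episode (mild, moderate, severe, or currently in remission") and whether the episode is single or recurrent.

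Under Settings and participants, a patient is eligible through a new diagnosis of major depression, or through a new antidepressant prescription linked to a prior diagnosis. Neither route requires a recorded severity.

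The Aim section lists "a) the quality and precision of the diagnosis of major depression" as an effectiveness domain and places initial treatment selection under domain (c). The INDI program section describes a guideline tool, built into the computerized records, that supports diagnosis and the recording of clinical status. The Discussion expects that "we will see substantial changes in the care process for depression in primary care". Under Analyses, indicators are compared pre-post and between intervention and control, and "we will work with the entire population and not with a sample".

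**The concern.** A patient with no recorded severity is eligible but belongs to neither adequacy row as worded. A patient coded in remission is also outside both. Who enters these two denominators therefore depends on a recording practice that the programme may change and that the study counts as an outcome. The comparison is then between groups selected on a post-intervention variable.

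Suppose recording rises under INDI, and patients who become scorable only because of INDI are treated differently from those scorable anyway. The adequacy proportion will then move although no prescribing decision has changed. The movement appears in the intervention-control contrast and in the pre-post contrast within INDI areas. Similarity of the areas at baseline does not protect against it, because the shift arises after implementation starts. At stake is the reading of initial treatment selection, one of the stated effectiveness criteria.

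**Working it through.** The article states no figure to reproduce: it gives no recording rate, no adequacy rate and no sample size. **All rates below are assumptions.** They show how the mechanism works and do not estimate its size in this study.

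**Set-up**, for the moderate-or-severe indicator, with no true effect of INDI on treatment:
- r0 = share of truly moderate or severe patients with severity recorded in the comparison setting (control area, or baseline)
- r1 = the same share under INDI, with r1 at least r0; patients recorded in the comparison setting are taken to be of a kind also recorded under INDI
- a1 = adequacy in patients recorded in either setting
- a2 = adequacy in patients recorded only under INDI

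**Formulas.** Scored adequacy is a1 in the comparison setting and [r0·a1 + (r1 − r0)·a2] / r1 under INDI. The artefact is the difference, (r1 − r0)(a2 − a1) / r1.

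| a1 | a2 | r0 | r1 | Comparison | INDI | Artefact (points) |
|---|---|---|---|---|---|---|
| 80% | 60% | 40% | 50% | 80.0% | 76.0% | −4.0 |
| 80% | 60% | 40% | 60% | 80.0% | 73.3% | −6.7 |
| 80% | 60% | 40% | 80% | 80.0% | 70.0% | −10.0 |
| 80% | 70% | 40% | 80% | 80.0% | 75.0% | −5.0 |
| 80% | 50% | 40% | 80% | 80.0% | 65.0% | −15.0 |
| 60% | 80% | 40% | 50% | 60.0% | 64.0% | +4.0 |
| 60% | 80% | 40% | 80% | 60.0% | 70.0% | +10.0 |
| 50% | 80% | 40% | 80% | 50.0% | 65.0% | +15.0 |
| 80% | 80% | 40% | 80% | 80.0% | 80.0% | 0 |
| 80% | 60% | 60% | 60% | 80.0% | 80.0% | 0 |

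Example, third row: (0.4 × 0.80 + 0.4 × 0.60) / 0.8 = 0.70. A milder contrast (80% and 70%, recording 40% against 50%) gives −2.0. The mild indicator follows the same formula with its own rates. It is scored on not prescribing, so its artefact could run the other way.

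**Would it be noticed?** Assume 500 truly moderate or severe patients per arm, so 200 scored in control and 400 under INDI, and ignore clustering. The −10-point artefact then reaches nominal significance with probability about 0.75.

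**Bounds**, third row. Comparison: 60% not recorded, so 0.4 × 0.80 = 32% up to 32% + 60% = 92%. INDI: 20% not recorded, so 0.8 × 0.70 = 56% up to 56% + 20% = 76%. The difference lies between 56 − 92 = −36 and 76 − 32 = +44 points. It includes zero, so the 10-point deficit would correctly not be put down to treatment.

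**A repair that fails.** Counting severity recorded and treatment adequate over everyone gives r0·a1 against r0·a1 + (r1 − r0)·a2, an artefact of (r1 − r0)·a2. In the third row this is 32% against 56%, a false gain of 24 points, larger than the 10 points it should remove. In the ninth row, where the scored-only comparison is unbiased, it is 0.4 × 0.80 = +32 points.

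**The case against.** **Denominators belong in the analysis plan, and this is a condensed article.** How to handle an unclassified record may well be specified there. But the article itself makes the two indicators depend on severity and makes recording severity an outcome, and that dependence stands whatever the plan adds.

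**Another severity source could be used.** Baseline PHQ9, or the complementary sources feeding the database, might supply a class. The article names neither for these rows. Baseline PHQ9 use is also an impact indicator, so its availability could differ between arms in the same way.

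**Part of this is already visible.** The diagnostic-accuracy row, compared by arm and period, gives some idea of recording, but it also requires single or recurrent status. The rate of antidepressant treatment and the anxiolytic row need no severity class, but they do not measure treatment matched to severity.

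**Stronger readings a reader might infer, which the documents do not support:**
- *Severity is often unrecorded at present.* The Background mentions inadequacies in diagnosis generally and says nothing about severity coding. That INDI will raise recording is an inference from the Aim, the record-integrated tool and the Discussion.
- *The analysis contradicts its whole-population statement.* That statement says records of all eligible patients are used. It does not promise one denominator for every indicator, and other Table 2 rows openly use subgroups. The intention-to-treat sentence concerns adherence to INDI.
- *INDI will look worse than it is.* The bias may be negative, positive or zero.
- *The in-remission group will shift too.* The first row counts that code as a specified severity, so it predicts no change there. These patients are simply outside both adequacy rows.

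**Conclusion.** The point holds in a limited form. As worded, the two adequacy indicators are compared in patients selected on a variable that INDI may change, so a difference cannot by itself be read as a change in treatment. The bias needs two conditions together: recording must differ between arms or periods, and adequacy must differ between patients recorded anyway and those recorded only under INDI. If either fails, it is zero. The article gives no figures for either condition, so the range of about 4 to 15 points in either direction rests wholly on assumed rates.

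The weight is moderate. Two of the 23 Table 2 indicators are affected, and the article names no primary endpoint, but they are the rows that match initial treatment to severity under domain (c). No view is taken on the treatment rules the indicators embody.

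**What to change.** For each of the two indicators:

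1. State the source of the severity class.
2. Report by arm and period the numbers adequate, inadequate, severity not recorded, and coded in remission, keeping the last outside the comparison.
3. Add sensitivity bounds that score the not-recorded group as all adequate and as all inadequate.
4. Read the result beside the severity-free rate of antidepressant treatment already in Table 2.
5. Do not attribute a difference in the scored-only proportions to changed treatment unless it survives the bounds, or recording is similar across arms and periods.

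Do not make severity recorded and treatment adequate, over all eligible patients, the arm comparison: it counts better recording as better treatment.

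The cost is some analysis wording and a few table rows from the same records. The bounds may be wide where much is unrecorded, and the indicator may then be inconclusive; in that case the wide bounds are the result to report.

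### PHQ-9 response and remission come from routine records, but INDI is expected to change PHQ-9 recording, so the planned clinical contrasts can show a difference that does not exist

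*Protocol article*

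**What the plan says.** All references are to the protocol article.

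- **Outcomes.** Under Quantitative evaluation, Table 2 defines response as "Proportion of patients who show a reduction ≥50% in their baseline PHQ9 score at 6 and 12 months" and remission as "Proportion of patients with a PHQ9 score < 5 points at 6 and 12 months". It also lists the evolution of PHQ-9, GAF and MINI suicide-risk scores.
- **Source.** Below the table: "These indicators will be obtained from the SIDIAP database", which draws on computerized primary care records. No outcome assessment outside routine care is described.
- **Recording as an effect of INDI.** The same table, which is the battery for measuring INDI's impact, contains "Number of times per patient in which a validated scale is used (PHQ9) in clinical follow-up", the use of the PHQ-9 at the baseline assessment, and the use of the MINI for baseline suicide risk.
- **The programme.** The Background calls systematic monitoring a key feature of collaborative care. Intervention (INDI program) adds a tool inside the clinical record that includes "systems for recording and retrieving information" on the patient's clinical status.
- **Usual care.** The Background says that monitoring of depression in primary care is seldom scheduled. Under Control, the control centers adopt no special practices.
- **Analysis.** The Analyses section plans pre-post and intervention-control comparisons of the indicators. It says that using all eligible patients' records rather than a sample helps to minimize selection bias and "is based on an independent data collection".

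**The concern.** A patient contributes to remission only if a PHQ-9 was entered at follow-up, and to response only if one was also entered at baseline. The plan expects INDI to change how often those entries are made. The exposure being compared is thus likely to influence who has an outcome at all, both between arms and between periods.

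Working with the whole eligible population does not cure this. It settles who is in the denominator, not who has a score. Intention-to-treat fixes group membership but supplies no missing scores. The baseline comparison of areas cannot detect a recording gap that implementation creates later. A larger record base narrows the confidence interval around a biased figure.

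At stake is the claim that INDI produces better clinical outcomes. That is one of the five effectiveness domains under Aim, and part of the basis on which generalization to the Catalan system would be proposed.

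**Working it through.** The article gives no sample size, event count or PHQ-9 coverage, so it has no figure of its own to reproduce. The arithmetic below shows only what the mechanism can do. **All rates in it are assumptions**, except the benchmark of 15–20% higher response and remission quoted from the earlier INDI trial under Intervention (INDI program).

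**Step 1. Which outcomes depend on recording.** Response needs a baseline and a follow-up PHQ-9. Remission needs a follow-up PHQ-9 only. GAF and MINI evolution need recorded scores. Together with PHQ-9 evolution, that is 5 of the 23 indicators in Table 2. PHQ-9 recording, and baseline MINI recording, are themselves indicators. GAF recording is not, so for GAF the argument rests on the data source alone.

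**Step 2. Only scored patients analysed.** Let p be the true rate, r1 and r0 the probabilities of being scored in responders and non-responders, and k = r0/r1.

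Observed rate = p·r1 / (p·r1 + (1 − p)·r0) = p / (p + (1 − p)·k)

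Only the ratio k enters; the level of coverage drops out. Take p = 40% in both arms, so that the true difference is 0, with coverage of about 70% in INDI and about 20% in control.

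| Recording pattern | INDI observed | Control observed | False difference |
|---|---|---|---|
| Unrelated to status in both arms | 40% | 40% | 0 |
| Non-responders scored 2× as often in both arms | 25% | 25% | 0 |
| Control non-responders 1.5× | 40% | 0.4/(0.4+0.9) = 30.8% | +9 points |
| Control non-responders 2× | 40% | 0.4/(0.4+1.2) = 25.0% | +15 points |
| Control non-responders 3× | 40% | 0.4/(0.4+1.8) = 18.2% | +22 points |
| Control responders 1.5× | 40% | 0.4/(0.4+0.4) = 50.0% | −10 points |
| Control responders 2× | 40% | 0.4/(0.4+0.3) = 57.1% | −17 points |
| INDI responders 1.5×, control unrelated | 50% | 40% | +10 points |

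**Step 3. Unscored patients counted as non-responders.** Observed rate = p × coverage, with recording unrelated to status.

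- Coverage 70% v 20%: 0.4×0.7 = 28% v 0.4×0.2 = 8%, a false +20 points.
- Coverage 60% v 40%: 24% v 16%, a false +8 points.
- Coverage 50% v 10%: 20% v 4%, a false +16 points.

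Here unequal coverage alone is enough. Table 2 does not say whether its patients are all eligible patients or only those with scores, so either analysis fits the text.

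**Step 4. What the data can say without assumptions about the unscored.** With coverage c and 40% observed among the scored, the all-patient rate lies between 0.4c and 0.4c + (1 − c).

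- c = 70%: 28% to 58%.
- c = 20%: 8% to 88%.
- The difference therefore lies between 28 − 88 = −60 and 58 − 8 = +50 points.

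**The case against.** The strongest reply is that the bias is conjectural. Several stronger readings are tempting, and the article does not support them.

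- **That INDI trains staff to use these scales or requires the PHQ-9.** The article mentions training components in general and a recording tool. The link to PHQ-9 recording is inferred from Table 2 and from the emphasis on systematic monitoring.
- **That control scores exist only for a sick or re-attending minority.** Seldom-scheduled monitoring says nothing about PHQ-9 coverage or which patients are scored. Control centers may also take up other quality initiatives, which could narrow the gap.
- **That unequal recording must bias the result.** Among scored patients it does not, if recording is unrelated to status or equally related to it in both groups. Shared dependence also shrinks the bias. With control non-responders scored 2.5 times as often (0.4/(0.4+1.5) = 21.1%), the false difference is 19 points if INDI recording is unrelated to status. It is 10 points if INDI shares a 1.5-fold dependence (30.8%), and 4 points if it shares a 2-fold one (25.0%).
- **That the claim of independent data collection is false.** It may mean independent of the research team, and the source cited for it is not at hand.

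It is also fair that the PHQ-9 use indicators will make part of any recording gap visible, that symptom, GAF and MINI evolution are labelled descriptive, and that missing-data methods may sit in an unseen analysis plan. The absence of such a method is not the point here.

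What remains is what the article itself fixes: an outcome source whose availability INDI is expected to change, comparative use of that source, and a reassurance about selection bias that does not extend to who is scored. The existing use indicators do not give the share of patients with a score at 6 or 12 months.

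**Conclusion.** The concern holds as a statement about mechanism. PHQ-9 response and remission, and the GAF and MINI evolution measures, are likely to be observed for different shares of patients by arm and by period. The planned contrasts can then be false under either of two conditions: recording depends on patient status differently between the groups, or unscored patients are counted as non-responders.

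Neither size nor direction can be derived from the document. Under the assumed 40% true rate, the false difference in scored patients runs from 0 to +22 or −17 points, and counting missing as failure at 70% v 20% coverage gives +20. These figures show that the artefact could be as large as the 15–20% benefit quoted from the earlier trial. They do not show that it will be. A reader might infer that the trial will manufacture a benefit for INDI; the article does not support that, since the error could run either way or be nil.

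The statement on minimizing selection bias is sound for eligibility and does not extend to score availability. Indicators that need no clinician-entered scale are not affected in this way.

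**What to change.** 1. **Show availability.** Beside each scale-based outcome, report the proportion of eligible patients with a PHQ-9, GAF or MINI score at baseline, 6 and 12 months, by arm and period.
2. **Qualify the contrast.** Do not count unscored patients as non-responders, except as one end of the bounds. Present any INDI-control or pre-post PHQ-9 contrast only with worst-case and best-case bounds and a sensitivity analysis weighted by the inverse probability of recording. Weighting corrects only for predictors held in the record. Make no unqualified claim of better clinical outcomes from these contrasts.
3. **Rest firm comparative conclusions on indicators that need no scale.** Prescription persistence, follow-up visits, and switch or augmentation qualify. Label them as care-process and not symptom outcomes, and note that INDI may also change who is diagnosed and hence who is eligible.
4. **Correct the Analyses wording.** Limit the selection-bias statement to eligibility, and say that data collection is independent of the research team, if that is what is meant.

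The cost is wording, one table and a sensitivity analysis, all from data already to be extracted. The downside is a more modest clinical conclusion. A PHQ-9 survey in both arms would address the problem more directly, but it is new fieldwork and not part of this fix: the planned questionnaires go to INDI patients only, at 12 months, with no baseline.
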